## Method

### Study design

The GrOup-based physical Activity for oLder adults (GOAL) Trial is a 3-arm randomized controlled trial (RCT) developed in alignment with the tenets of self-categorization theory. The study has been approved by the Behavioral Research Ethics Board at The University of British Columbia, and is registered with ClinicalTrials.gov (# NCT02023632).

The design, conduct, and reporting of this study will adhere to the Consolidated Standards of Reporting Trials (CONSORT) guidelines [36]. The pre-screening process included the completion of the Physical Activity Readiness Questionnaire for Everyone (PARQ+) and Electronic Physical Activity Readiness Medical Examination (ePARmed-X+) [37]. Pre-screening was conducted either by a trained research assistant or the project coordinator (authors [name] and [name]) using a pre-screening script for consistency. If the ePAR-medX+ highlighted that the interested older adult needed physician approval prior to joining the program, the research assistant informed the individual and indicated that subsequent physician approval was required before s/he then could enroll in the study. Following the initial screening process for inclusion/exclusion, informed consent was obtained, and participants were randomized to one of three study arms:Similar-Age Same-Gender (SASG)Similar-Age Mixed-Gender (SAMG)Mixed-Age Mixed-Gender (MAMG)

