### Study interventions

The trial is taking place at three different YMCA centers in the Lower Mainland of British Columbia, over 2 years. The group exercise classes take place in 3-month blocks with the opportunity to re-enroll in the same program for another 3 months, thus lasting 6-months in total (see Fig. 1). Each program is run on the basis of classes taking place three days per week, with classes lasting 50–60 min. This dosage (150–180 min/week) is consistent with Canada’s current physical activity guidelines for older adults engaging in ≥ 150 min of moderate-to-vigorous physical activity per week [38], as well as findings from the Canadian Community Health Survey [39] which found that 67 % of seniors who are active three or more times a week are in good health, compared to 36 % who are infrequently active.

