##### General health status

Data were collected in relation to participants’ smoking status, general health status, previous history of illness, and current use of medication.

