#### Sample size

We powered our study to detect significant differences in individuals’ physical activity adherence (over 3 and 6 months) in the SASG groups when compared to the SAMG and MAMG standard care control condition. In order to detect a medium effect size *f* = .25 (difference between the SASG and both SAMG and MAMG conditions) based on a 2 (Gender) x 3 (Conditions) ANCOVA with the percentage of classes attended over three and six months specified as dependent variable (while controlling for baseline levels of physical activity) with power (1 - β) set at .80, and alpha set at .05, 211 participants were required across the 3 centers [59]. In order to conduct a logistic regression analysis based on individuals’ re-enrollment across the three group-based programs, based on power at .80, alpha at .05, an anticipated medium effect size (odds ratio = 2.5), and a balanced design, 167 participants were required [59].

To test for mediation through use of a cross-lagged panel model based on a structural equation modeling (SEM) approach, while modeling gender invariance, we drew from three broad criteria. First, based on recommendations provided by MacCallum et al. [60], and using Preacher and Coffman’s [61] R-code for assessing RMSEA (< .05), based on power set at .80, a minimum sample size of 163 was identified as being necessary for conducting the cross-lagged panel model (without considering gender differences). This calculation approximates with recommendations provided by Garver and Mentzer [62] that a ‘critical sample size’ of 200 is required as a general rule of thumb for providing sufficient statistical power for SEM analysis. In addition to these two sets of considerations, in light of the fact that the panel model will include a *multi-group* (males, females) component in order to examine gender invariance, this requires twice the sample size (i.e., *n* = 326, cf. MacCallum et al.; *n* = 400, [60]). Thus, in order to account for an attrition rate as high as 25 % (over the course of the program) a sample size of 540 would be sufficient to examine the mediational model proposed in this trial. In sum, we determined that an overall sample size of 540 older adults across the three arms of the trial would be sufficient for examining each of the study hypotheses.

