#### Proposed outcome analyses

Preliminary analyses will be conducted to examine whether any patterns of missing data exist (e.g., missing at random, missing completely at random, etc.) for each of the psychosocial variables (cohesion, affective attitudes) using the Missing Value Analysis (MVA; examination of Little’s chi square test) on SPSS Version 20. The data will also be examined for multivariate and univariate outliers, as well as for violations of normality, with the appropriate transformation procedures utilized. Prior to the main analyses, we will also examine invariance in the primary outcome variable (adherence over 3 and 6 months) across the two cohorts (cohort 1 – March to August 2014; cohort 2 – March to August 2015). In light of the fact the two cohorts will be examined at exactly the same time of year, using exactly the same experimental procedures, we would expect invariance in patterns of adherence across the three conditions in each year, thus supporting the pooling of data from both cohorts. Two 2 (gender) x 3 (conditions) ANCOVAs with baseline measures of physical activity (LTEQ scores) entered as a covariate, and adherence to the program over 3-months and 6-months as the dependent variable.

A logistic regression analysis will be conducted to examine the likelihood of older adults randomized to the SASG condition re-enrolling in the same SASG condition after the initial 3-month program, when compared to the re-enrollment of older adults in the SAMG and MAMG conditions. In the logistic regression model, gender will be added as an independent variable, with the regression model explained by $$ \pi =\frac{1}{1-{e}^{-x}} $$ where x = *b0* + *b1G1* + *b2 G2* + *b3 gender* + *b4G1*gender + b5G2*gender* (where *b0* is the intercept and *b1*-*b5* are the slopes for predictors). For hypotheses 1, 2, and 4, SPSS Version 20 will be used to analyze the data.

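### The re-enrolment model adjusts for no baseline value except gender, not even LTEQ, and the adherence ANCOVAs leave out the collected health status: a small, nearly free efficiency gain is passed over

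*Protocol article*

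**What the plan says.** Under Proposed outcome analyses, the protocol article plans two gender-by-condition ANCOVAs of adherence, at 3 and at 6 months, "with baseline measures of physical activity (LTEQ scores) entered as a covariate". LTEQ is the only covariate named. The Sample size section matches this: the ANCOVA calculation is described as made "while controlling for baseline levels of physical activity".

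For re-enrolment the same section says "In the logistic regression model, gender will be added as an independent variable" and then prints the linear predictor: an intercept, two condition indicators, gender, and the two condition-by-gender products. There is no LTEQ term and no other baseline value.

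The General health status section lists smoking status together with "general health status, previous history of illness, and current use of medication". The Outcomes section places the general health and physical activity questionnaires at the baseline assessment in the last week of February, before classes begin in March. Age is collected too (Demographic and background measures).

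The Study interventions section supports the three-day class schedule with a national survey finding that "67 % of seniors who are active three or more times a week are in good health, compared to 36"% of those infrequently active.

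**The concern.** The covariate sets are written out, so this is a choice fixed in the protocol and not a detail left to an unseen analysis plan. Two things stand out.

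First, the models are inconsistent. The protocol treats baseline activity as worth adjusting for when the outcome is attendance (Hypothesis 1), but drops it when the outcome is signing up for a second block of the same classes (Hypothesis 2, and the re-enrolment part of Hypothesis 4). It gives no reason for the difference.

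Second, general health status is measured before classes start and could plausibly predict whether an older adult keeps coming to class, yet neither model uses it.

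A pre-specified prognostic baseline covariate reduces residual variance in a linear model, usually raises power in a logistic model, and allows for chance imbalance between arms. What is at stake here is efficiency, not validity.

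**Working it through.** **Inputs from the protocol article.** f = .25, power .80, alpha .05, N = 211 for the 2 × 3 ANCOVA; 540 enrolled and attrition up to 25%, so 540 × 0.75 = 405 retained; odds ratio 2.5 for re-enrolment (all Sample size). Survey proportions 67% and 36% (Study interventions). The documents give no R² for LTEQ or for health status, and no reference re-enrolment rate.

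**1. Reproducing the plan's figure.** The protocol states "In order to detect a medium effect size *f* = .25" and "alpha set at .05, 211 participants were required across the 3 centers". Using the noncentral F with λ = f²N and denominator df = N − 6 − (number of covariates), a 5-df numerator with one covariate gives power .798 at N = 210 and .800 at N = 211. The stated 211 is reproduced. The condition effect alone (2 df) needs 158.

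**2. Effect of adding health status to the ANCOVA.** Let R² be the share of residual variance that health explains *after* LTEQ, gender and condition. The standard error is multiplied by √(1 − R²), and f becomes f/√(1 − R²). R² is assumed.

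| Extra R² (assumed) | SE multiplier | N needed (5 df, f = .25) | Power, condition effect (2 df), f = .25, 405 retained | Same, f = .15 |
|---|---|---|---|---|
| 0 (as planned) | 1 | 211 | .997 | .773 |
| 0.01 | √0.99 = 0.995 | 209 | .997 | .777 |
| 0.02 | √0.98 = 0.990 | 207 | .997 | .782 |
| 0.05 | √0.95 = 0.975 | 201 | .998 | .795 |

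The rows with extra R² use two covariates in place of one. The lost degree of freedom does not show at this precision.

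**3. What the survey figure can carry.** As a 2 × 2 table, 67% against 36% is an odds ratio of (.67/.33)/(.36/.64) = 3.61. It relates health to general activity. It is not conditional on LTEQ, so it does not supply the R² needed in step 2.

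**4. Effect in the logistic model.** Checked by simulation: three equally likely arms, a binary health variable with 50% prevalence, one active arm differing from reference by the treatment odds ratio, gender as a main effect, 405 participants, 1,500 runs per setting. The baseline rate, the health prevalence and both health odds ratios are assumptions. The value 3.6 is carried over from the survey and is likely optimistic.

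| Treatment OR | Health OR | SE of log OR, unadjusted → adjusted | Mean log OR, unadjusted → adjusted | Power, unadjusted → adjusted |
|---|---|---|---|---|
| 2.5 | 3.6 | .252 → .266 | .839 → .932 | .921 → .941 |
| 2.5 | 2.0 | .253 → .258 | .897 → .927 | .942 → .949 |
| 1.7 | 3.6 | .247 → .262 | .489 → .545 | .512 → .550 |
| 1.7 | 2.0 | .248 → .253 | .524 → .542 | .563 → .577 |

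Adjustment moves the log odds ratio away from zero by proportionately more than it raises the standard error. Power therefore rises while the standard error does not fall. The simulation adds health only; what LTEQ would add to this model was not simulated and cannot be sized from the documents.

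**The case against.** The strongest reply is that nothing here is wrong. The protocol pre-specifies a baseline covariate close to the outcome, uses it consistently between the ANCOVA and its sample size, and loses neither unbiasedness nor type I error control by stopping there. A further covariate is optional, and at the planned effect size the adherence test has almost nothing left to gain. All of that stands, and it limits the point to a minor improvement. It does not explain why LTEQ is in one model and absent from the other.

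Several stronger readings are tempting, and the documents do not support them:

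- *The survey shows that health predicts this outcome.* It does not. The figure reports health by general activity level and is used to justify the class schedule. The outcome is attendance at offered classes among volunteers who passed screening ("The pre-screening process included the completion of the Physical Activity Readiness Questionnaire for Everyone"), so the range of health is probably narrower. LTEQ already measures the activity side of the link. The figure makes health plausibly prognostic and no more.
- *The survey association can be turned into a saving in participants.* That would carry an unadjusted association with another behaviour over unchanged as the R² for attendance beyond LTEQ.
- *Age should be a required covariate as well.* No section links chronological age to attendance or re-enrolment among people aged 65 and over. The age findings in the Background concern similarity within groups.
- *Omission makes the re-enrolment estimate less precise.* The simulation shows the reverse for the standard error.
- *The pre-screening clearance result could stand in where health status is missing.* That would mix two different measures in one covariate, and the protocol does not say that clearance is kept as a data item.

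One caution remains. The Trial status section lists randomisation before baseline measures, so self-reported health may have been recorded after allocation, though before classes. The same applies to LTEQ.

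**Conclusion.** The point holds as a minor, optional efficiency improvement. It is clearest for re-enrolment, where the printed model omits even the covariate the protocol uses for adherence. For adherence, adding general health status would cut the standard error by about 0.5% to 2.5%, if it explains 1% to 5% of residual variance beyond LTEQ. That makes no practical difference at f = .25 and adds up to about two percentage points of power at f = .15 with 405 retained. For re-enrolment, the simulated power gain from health ranges from under one to about four percentage points, and the upper end depends on an odds ratio borrowed from a different setting. The randomised comparison is not biased either way. These sizes rest on assumed prognostic strength, because the documents give none. No conclusion of the trial is put at risk by leaving the models as they are.

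**What to change.** Pre-specify LTEQ and baseline general health status as covariates in the re-enrolment logistic model, and add general health status beside LTEQ in both adherence ANCOVAs. Name the single health-status score to be used and its coding. State that the adjusted odds ratio is conditional on these covariates, so that it is not compared directly with an unadjusted one. Age may be added as an option, on the understanding that the documents give no evidence for it. Confirm whether the baseline questionnaires were completed before participants knew their allocation.

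The cost is a sentence or two in the analysis plan and, with health status entered as one score, one degree of freedom in each ANCOVA and two in the logistic model. The Trial status section says that no data from either cohort have been analysed, so the covariates can still be fixed in advance. Added after results are seen, they would look selective.

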### Aims and hypotheses

Drawing from the tenets of self-categorization theory and previous observational research our primary research question was concerned with whether older adults sustain their involvement in physical activity programs (over three and six months) when they participate in groups that are comprised of members of a similar age and same gender, relative to those taking part in similar-age but mixed-gender classes. Both of these conditions will be compared to the adherence of older adults within standard (mixed -age mixed-gender) ‘control’ physical activity groups. Second, we were interested in whether, at the end of a 3-month physical activity program, older adults in SASG (similar-age same-gender) classes will re-enroll in SASG classes over the following 3-month period (6 months in total) to a greater extent when compared to older adults in the SAMG (similar-age mixed-gender) and MAMG (mixed-age mixed-gender) conditions. Our third research question was concerned with whether any group differences among these adherence outcomes can be explained through a mediation model (with cohesion and affective attitudes as target mediators). Our fourth research question was concerned with whether there are gender differences across the primary outcome (physical activity adherence behavior) by assigned condition. Consistent with our previous findings that women demonstrate a slightly stronger preference for same-gender contexts [19] we expected that (in addition to main effects for the SASG context when compared to the mixed-gender settings), the effects for SASG versus the other two conditions (in relation to adherence) would be more pronounced for women. The following hypotheses will be tested:*Hypothesis 1.* Older adults in the SASG groups condition will demonstrate improved adherence (i.e., attendance rates) over 3-months and 6-months than older adults in the SAMG condition, who in turn will demonstrate improved adherence to those older adults in a standard (control) group-based exercise condition (MAMG).*Hypothesis 2.* A greater proportion of older adults in the SASG condition will re-enroll in the program (after 3 months for an additional 3 months; 6 months total) than those in the SAMG and MAMG groups.*Hypothesis 3.* The covariance of the assigned conditions (SASG, SAMG, MAMG) on adherence (at 3 and 6 months) will be explained (mediated) by changes in older adults’ perceptions of group cohesion and affective attitudes (enjoyment).*Hypothesis 4.* Gender will moderate the effects of the intervention conditions in relation to adherence and re-enrollment.

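### The printed re-enrolment model includes both condition-by-gender products and names no contrast for Hypothesis 2, so under 0/1 gender coding its condition coefficients describe one gender only

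*Protocol article*

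**What the plan says.** Hypothesis 2 (Protocol article, Aims and hypotheses) is about the whole trial population: "A greater proportion of older adults in the SASG condition will re-enroll in the program" than in the two mixed-gender arms. Hypothesis 4 is separate: "Gender will moderate the effects of the intervention conditions in relation to adherence and re-enrollment". The text leading up to the hypotheses gives the expected direction for adherence, namely that the SASG advantage "would be more pronounced for women".

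Under Proposed outcome analyses, one logistic regression is described. Its purpose is to examine re-enrolment in SASG "when compared to the re-enrollment of older adults in the SAMG and MAMG conditions". The model is introduced with the words "In the logistic regression model, gender will be added as an independent variable, with the regression model explained by", followed by the link and the linear predictor. The linear predictor is "x = *b0* + *b1G1* + *b2 G2* + *b3 gender* + *b4G1*gender + b5G2*gender", and the only gloss on the coefficients is that b0 "is the intercept and *b1*-*b5* are the slopes for predictors". The article prints no second model without the products. It does not say how gender, G1 and G2 are coded, and it names no contrast as the test of Hypothesis 2. The link is printed as 1/(1 - e^-x).

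Under Sample size, the re-enrolment calculation uses an odds ratio of 2.5, power .80, alpha .05 and a balanced design, and arrives at 167 participants.

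**The concern.** Once products with gender are in the model, a condition coefficient is no longer an overall effect. It is the effect at the point where gender equals zero. With 0/1 coding, the usual choice for a binary covariate, that point is one of the two genders.

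An analyst who follows the printed equation and reads the condition rows of the output would therefore test Hypothesis 2 in men only or in women only. If the effect differs by gender, as Hypothesis 4 predicts, the two choices give different answers from the same fit. Even if the effect does not differ, the test uses only the people in one gender for each comparison and loses power. At stake is the clarity and efficiency of the test for a named hypothesis that has its own sample-size calculation.

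**Working it through.** **Inputs from the article.** 540 participants over three arms, with a target of half women (Participants); odds ratio 2.5, power .80, alpha .05 (Sample size).

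**Assumptions.** Equal allocation, so 540/3/2 = 90 per arm-gender cell; two-sided alpha; comparator re-enrolment p0 = 50%, because the article gives no base rate (30% and 70% are shown as a range).

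**1. The plan's own figure.** For one balanced binary predictor without interaction, the Wald formula is N = (1.960 + 0.842)² × [1/(0.5·p0(1-p0)) + 1/(0.5·p1(1-p1))] / (ln OR)². With p0 = 0.50 and OR 2.5, p1 = 0.714. This gives 7.849 × (8 + 9.8) / 0.8396 = 166.4, rounded up to 167. The stated figure reproduces, for a two-group comparison without products.

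**2. What the coefficients mean.** In the printed predictor the log odds ratio for G1 is b1 + b4·gender, and for G2 it is b2 + b5·gender. So b1 and b2 are the effects at gender = 0. Under 0/1 coding that is one gender. Under -1/2, +1/2 coding (or -1, +1) it is the midpoint, and b1 and b2 are equally weighted gender averages.

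**3. Power with the same effect in both genders (OR 2.5, ln OR = 0.916).**
- One gender, 90 v 90: variance = 1/(90 × 0.25) + 1/(90 × 0.2041) = 0.0444 + 0.0544 = 0.0989; SE 0.314; z = 2.914; power = Φ(2.914 - 1.960) = 83.0%.
- Averaged over genders: variance 0.0989/2 = 0.0494; SE 0.222; z = 4.121; power = Φ(2.161) = 98.5%.
- Range over the base rate: at p0 = 30% (p1 = 0.517, one-gender variance 0.0974), 83.5% against 98.6%; at p0 = 70% (p1 = 0.854, variance 0.1419), 68.2% against 93.1%.

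**4. Dependence on the code when effects differ.** As an illustration, assume SASG odds ratios of 1.3 in men and 2.5 in women against either comparator arm, with p0 = 50% and 90 per cell. The printed model, with SASG as reference, was fitted to the expected counts:

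| Gender coding | b1 = b2, as OR | p |
|---|---|---|
| men 0, women 1 | 0.77 (= 1/1.3) | 0.38 |
| women 0, men 1 | 0.40 (= 1/2.5) | 0.0036 |
| -1, +1 | 0.555 | 0.0066 |

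The log-likelihood is the same in every fit (-364.99). The gender-averaged contrast is OR 0.555, p = 0.0066, under every coding. Power is 14% with men coded 0, 83% with women coded 0, and 77% for the averaged contrast.

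**5. A wider gap, under a stronger assumption.** The Background reports preference effects of d = .76 for women and .30 for men. Converted by exp(d·π/√3), these are odds ratios of 3.97 and 1.72. If preference effects carried over to re-enrolment, power would be 43% with men coded 0, 98% with women coded 0, and 99% averaged.

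**6. The link.** 1/(1 - e^-x) gives 1.58 at x = 1 and -0.58 at x = -1, so it is not a probability. The logistic form is 1/(1 + e^-x).

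**The case against.** The article never says that b1 or b2 decides Hypothesis 2. The printed model is saturated in condition and gender, so the gender-averaged SASG contrasts can be estimated from it and do not change with coding, as step 4 shows. A condensed article may also leave coding, reference arm and contrasts to a fuller plan, and the way the comparison is framed fits SASG as the reference already. All of this stands. A reader might infer that no term in the model can test Hypothesis 2; the documents do not support that.

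A reader might also infer that the sign of the result could reverse. That would need gender entered as a number coded 1 and 2, with b1 then read as the condition effect. Nothing in the article suggests it: the only coding it gives, for the outcome, is 1/0.

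The sizes need care too. At the planned odds ratio and a 50% base rate, even the one-gender test has 83% power, above the .80 target. The 43% figure rests on carrying stated preferences over to behaviour. Taking 25% attrition off the sample (405 people, 67.5 per cell) would give 71.3% against 94.6%, but that case is doubtful: re-enrolment comes from enrolment records, so a dropout would normally count as a 0, not as missing, and the article states the attrition allowance when sizing the mediation model.

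Finally, the link error does not affect a logistic regression run in SPSS, which does not use the printed formula.

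What the objection does not remove is that the article chose to print an equation, and that its only condition terms, read in the usual way, answer a one-gender question.

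**Conclusion.** The point holds in a limited form. The printed model carries both products without naming a contrast for Hypothesis 2. Under 0/1 coding, its condition coefficients are effects in one gender, while the hypothesis is about everyone and the plan itself expects a gender difference. Reading Hypothesis 2 from them would tie the result to an arbitrary code and lose power: 83% against 98% at OR 2.5, a 50% comparator rate and 90 per cell, or 68% against 93% if the comparator rate were 70%. The algebra needs no assumption; the power figures rest on the assumed base rate, equal cells and a two-sided test.

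Severity is moderate. Re-enrolment is the second research question, and the defect lies in how the coefficients would usually be read, not in what the model can estimate. The attendance ANCOVAs are not affected in this way, because a factorial main effect averages over gender. The link is a notational error only.

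**What to change.** State the test of Hypothesis 2 in one of two equivalent-in-purpose ways:
- fit condition + gender without the products, and test SASG v SAMG and SASG v MAMG there; or
- keep the printed model, code gender -1/2, +1/2 with SASG as reference, and declare that b1 and b2, now gender-averaged, are the two contrasts.

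Reserve b4 and b5 for Hypothesis 4 and test them jointly. Define G1, G2 and the gender code where the equation is printed, and correct the link to 1/(1 + e^-x).

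The cost is a few lines of text and no new data. The Trial status section reports that no data from either cohort had been analysed when the article was submitted, so at that stage the choice can be fixed without knowledge of results.

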#### Outcomes

All pre-screening measures took place in January and February (2014 for cohort 1 and 2015 for cohort 2). Baseline physical health and fitness assessments were conducted in the last week of February, at which point participants also completed questionnaires designed to measure demographic and background variables, physical activity, general health status, as well as a measure of participant personality. In weeks 2, 7, 12, 14, 19, and 24 of the intervention (March to August) participants completed questionnaires that included measures of cohesion, instrumental and affective attitudes, task and self-regulatory self-efficacy, stigma consciousness and psychological flourishing. At week 2 and 14 assessments the questionnaire battery also included measures of intra-group perceptual similarity, commute time, and commute mode. At week 7 and 9, the questionnaire battery also included measures of intra-group communication and group interaction processes. In weeks 12 and 24, the questionnaire battery also included measures of participants’ physical activity behavior outside of their respective YMCA programs. Measures of program adherence were obtained throughout the course of the respective six-month programs. At the end of the respective six-month programs, participants completed the same physical health and fitness assessments as those completed at baseline, at which point the process evaluation interviews were also conducted.

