Mediation will be tested through use of a multi-group (to examine whether the effects are invariant across gender) cross-lagged panel model using a structural equation modeling (SEM) framework. Cross-lagged panel models are a type of auto-regressive modeling. This approach was proposed by Cole and Maxwell [64] for longitudinal data and will be adapted for the purpose of the present study. This approach has two advantages. Specifically, it allows us to examine the reciprocal relations between the mediators (cohesion and affective attitudes), and the outcome (adherence). In a recent paper we indicated the importance of assessing group cohesion throughout the lifespan of a physical activity group, and not just through a single time-point early-program measure (this has been the most commonly used method of assessing cohesion as a mediator within group dynamics physical activity research [65]). This panel modeling approach, in which all the variables are measured at multiple time points, can rigorously test the prospective relations between predictors (assignment to experimental condition), mediators, and outcomes (i.e., predictors prior to mediators and mediators prior to outcomes). The cross-lagged panel model will be estimated using Mplus 7.2 with a full information maximum likelihood (FIML) estimator used to handle missing data [66]. This procedure will use all available data points for parameter estimation under the assumption that the data are missing at random. FIML estimation tends to produce less biased estimates than deletion or simple missing data imputation techniques (e.g., EM algorithm, regression, listwise/pairwise deletion, mean replacement) even when data are not missing at random [67]. By examining multi-group models, this will allow us to examine whether the structural pathways are invariant across genders.

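### The Hypothesis 3 panel model is credited with a rigorous mediation test, but its mediator-to-adherence path is not randomised and, as described, is not adjusted for stable differences between people

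*Protocol article*

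**What the plan says.** Hypothesis 3 (Aims and hypotheses) reads: "The covariance of the assigned conditions (SASG, SAMG, MAMG) on adherence (at 3 and 6 months) will be explained (mediated) by changes in" perceptions of group cohesion and affective attitudes. Under Proposed outcome analyses the test is a multi-group "cross-lagged panel model using a structural equation modeling (SEM) framework", with gender as the grouping variable. The same paragraph adds: "Cross-lagged panel models are a type of auto-regressive modeling". It says that a published approach "for longitudinal data and will be adapted for the purpose of the present study", without describing the adaptation. It then claims that the model "can rigorously test the prospective relations between predictors (assignment to experimental condition), mediators, and outcomes", and the reason given is temporal order: predictors come before mediators, and mediators before outcomes.

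The paragraph names no pre-intervention covariate and no person-level term. Baseline activity appears under the same heading only for Hypothesis 1: "ANCOVAs with baseline measures of physical activity (LTEQ scores) entered as a covariate". On timing, Outcomes states: "In weeks 2, 7, 12, 14, 19, and 24 of the intervention (March to August) participants completed questionnaires that included measures of cohesion". Attendance comes from access cards and is recorded throughout.

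**The concern.** Mediation needs two links. Condition to mediator is a randomised comparison. Mediator to adherence is observational, because nobody is randomised to a level of cohesion or enjoyment. A person who is habitually active, sociable or healthy may both like the class more and attend more. Holding the previous attendance score fixed removes such a disposition only partly, because one score is an imperfect measure of it. The remainder appears as a positive cross-lagged path. Measuring the mediator before the outcome does not help, because the disposition precedes both.

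The protocol treats adherence as depending on prior activity, since it adjusts the Hypothesis 1 analyses for it. Hypothesis 3 is the trial's test of its explanatory theory, and the Discussion hopes to learn about mechanisms for wider implementation. Cohesion or enjoyment could be credited with an effect that belongs to pre-existing differences between people.

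**Working it through.** **The plan's own figure.** Sample size takes 200 per gender group, so 2 × 200 = 400. With 25% attrition, 400 / 0.75 = 534, against the 540 stated. Conversely 540 × 0.75 = 405. The sample size is not at issue; 405 is used below as the number analysed.

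**Inputs.** From the protocol: alpha .05, six mediator waves, 405 analysed, about 200 per gender group. Assumed, because the document gives none: share of variance that is a stable trait, τ = .5; within-person autoregression, φ = .3; correlation r between the mediator trait and the attendance trait; condition effect on the mediator, 0.5 SD. The true mediator-to-adherence effect is set to 0.

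**Closed form for one lag, unit variances.** Let c = τr (mediator with attendance) and s = τ + (1 − τ)φ (attendance with its own lag). Regressing attendance on the lagged mediator and lagged attendance gives:

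- spurious path b = c(1 − s) / (1 − c²)
- autoregressive path b_Y = (s − c²) / (1 − c²)
- residual variance v = 1 − (b·c + b_Y·s)
- SE = √[v / (N(1 − c²))]

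At r = .3: c = .15 and s = .65. So b = .15 × .35 / .9775 = .0537, b_Y = .6275 / .9775 = .642, v = .575, SE = √[.575 / (405 × .9775)] = .0381 and z = 1.41. The path is falsely significant with probability Φ(1.41 − 1.96) = .29.

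At r = .2: b = .10 × .35 / .99 = .0354, SE = .0379, z = 0.93, probability .15.

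At r = 0: b = 0, probability .05.

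**Six waves with lags held equal.** Five lags are pooled, so the SE falls by about √5. Then z = 3.15 at r = .3 (probability .88) and 2.09 at r = .2 (probability .55).

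**Monte Carlo.** These runs require both the condition-to-mediator and the mediator-to-adherence path to be significant. They agree with the closed form (τ = .5, φ = .3 to .4, N about 400):

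| Trait correlation | Single lag | Six waves, equal lags |
|---|---|---|
| 0 | 4-6% | 3-5% |
| .2 | 14-16% | 48-55% |
| .3 | 25-31% | 80-90% |
| .2, one gender group of 200 | about 10% | about 29% |
| .3, one gender group of 200 | about 14% | about 52% |

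**Sensitivity at r = .3, N about 400.**

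- With a trait share of .3, the rates are 15-17% (single lag) and 55% (equal lags).
- If condition does not move the mediator, false mediation with equal lags is 4.7%, although the mediator-to-adherence path alone is still falsely significant in 82% of runs. With a condition effect of 0.3 SD, false mediation is 49%.
- Adding LTEQ lowers the single-lag rate from 31% to 25% in one run (LTEQ assumed to correlate .5 with the attendance trait) and from 31% to 18% in another; in the latter the equal-lag rate falls from 90% to 77%. The gain depends on how closely LTEQ tracks the dispositions, which is unknown.
- A random-intercept term lowers the equal-lag rate from 82% to 5.0% (N = 405) and from 93% to 4.5% (N = 540), in 200 runs each.

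The simulations use one mediator and no other covariates.

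**The case against.** Five arguments deserve weight.

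1. The inflation is conditional on correlated traits. The LTEQ covariate shows that the authors expect adherence to vary with prior activity, not that this variation goes with cohesion. This stands: the size is a range under assumptions, not a forecast.

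2. The largest rates need lags held equal across waves, which the protocol never states. The gaps between weeks 2, 7, 12, 14, 19 and 24 are 5, 5, 2, 5 and 5 weeks and span the re-enrolment break, and the model is split by gender. This stands too, so the single-lag and per-gender figures are shown beside the pooled ones.

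3. A random-intercept model answers a different question. Every mediator wave follows randomisation, so a stable level of cohesion may itself be what the assigned class produced. In 80 simulated runs in which stable cohesion truly caused adherence, the random-intercept test rejected in 5% (N = 400) and the ordinary model in 89%. Power can also suffer: with no trait, persistent variables and a true path of .06, it was 69% against 98% at N = 400 and 44% against 81% at N = 200. A reader might infer that the planned model should be replaced. The documents do not support that, because Hypothesis 3 is not confined to within-person change around a stable level.

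4. An article summary may omit covariates or a trait term that the full plan contains, and the announced adaptation could cover one. So the silence is not an exclusion. What remains is the positive claim of rigour, which the text rests on time ordering alone.

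5. Hypotheses 1 and 2 do not depend on this model. That is correct and limits the consequence to the explanatory conclusion.

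**Conclusion.** The point holds in conditional form. The model as described does not justify an unqualified claim to test mediation rigorously, because its second link rests on an unstated assumption of no unmeasured stable confounding. If that assumption fails and condition moves the mediator, the false-mediation rate exceeds the nominal 5%: moderately for a single lag, and severely if lags are pooled. If the traits are uncorrelated there is no inflation.

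It would be too strong to say that the test will find mediation falsely. Trait share, trait correlation, autoregression and condition effect are all assumed, and nothing in the protocol shows that stable dispositions link cohesion or enjoyment with attendance. The change is worth making because it alters what Hypothesis 3 may conclude; it does not touch the adherence or re-enrolment comparisons.

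**What to change.** In the mediation paragraph of Proposed outcome analyses:

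1. Add baseline LTEQ, already collected and already the Hypothesis 1 covariate, as a predictor in the mediator and attendance equations. State that it removes only part of any such bias.
2. Keep the planned model, and prespecify a random-intercept cross-lagged model as a sensitivity analysis. State that it targets within-person effects only, would not detect mediation through a stable level of cohesion, and has less power. Six mediator waves, with attendance counted between them, are enough to attempt it.
3. Replace the claim of rigour with a statement that the mediator-to-adherence path assumes no unmeasured stable confounding. Claim mediation without qualification only if both models agree; otherwise report an association.

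The cost is some additional Mplus code and text, with no new data or participants. Trial status reports that no data had been analysed, so at the time of the article this could still be prespecified. The downsides are possible non-convergence of the second model and a more cautious conclusion on Hypothesis 3, including some cases where mediation through stable cohesion is real but the two models disagree.
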